### Early discontinuation/withdrawal of participants

A participant may choose to not start or to discontinue trial treatment early at any time before or during trial treatment or to withdraw from future participation in the trial at any time. This may be done without necessarily giving a reason, and without any personal disadvantage and without affecting their usual clinical care. An investigator may choose to discontinue trial treatment early (eg, due to toxicities) or to stop the participation of a participant after consideration of the benefit/risk ratio. Possible reasons are: (1) continued non-compliance with the trial protocol, (2) technical grounds (eg, participant moves) and (3) early termination at the request of the CI/PI. A reason must be provided for investigator decisions.

Discontinuation of trial treatment (participant or investigator decision) does not automatically entail withdrawal from the trial. Participants who discontinue trial treatment early are expected to continue with the follow-up assessments and sample collection per protocol, as part of the intention-to-treat analysis. Discontinuation from trial follow-up visits should be the last possible solution. Participants that withdraw after randomisation will not be replaced. Trial treatment discontinuation or participant withdrawal and the reason (where available) will be documented in the eCRF. In cases of withdrawal, permission to retain samples and data already collected will be documented in the eCRF.

### ATG preparation, dose and administration

Trial treatment infusions (intravenous) will take place over two consecutive days. ATG (Thymoglobuine) used in this trial must be stored, handled, prepared and dispensed as detailed in the current SmPC.^22^ This includes the requirement for administering Investigational medicinal product (IMP) and observing the participant in a hospital setting under medical supervision. Medical personnel and equipment must be readily at hand to provide emergency treatment if necessary, including in case of anaphylaxis. The diluent must be 0.9% sodium chloride; neither dextrose nor glucose solutions are permitted for this T1D trial population. Concomitant medication with hydrocortisone, heparin, and premedication with corticosteroid, antihistamine and paracetamol/acetaminophen is recommended, according to local procedures for ATG infusion to minimise the risk of expected ARs.

All participants of the trial will be under strict medical supervision for the duration of each infusion and carefully monitored before, during and after the infusions. Participants will be discharged no sooner than 2 hours after finishing the trial treatment infusions, or according to the investigator’s clinical judgement. In the event of early trial treatment discontinuation, or if the maximum of 60 hours has been reached without completing the second infusion, trial treatment can be discontinued without gradual tapering of the dose as per.^22^

### Placebo

Placebo will be an identical volume of sodium chloride 0.9%. Premedication requirements for placebo treatment are the same as for active IMP to maintain the blind for participants and the investigator/nurse (concomitant medication and premedication can affect blood glucose). Placebo will come from local hospital stock. Pharmacies will be responsible for applying the trial-specific labelling to placebo (and ATG) infusion bags and participant-specific details will be added to the labelling prior to dispensing. More information on the legal status, accountability and supply of the IMP/Placebo can be found in online supplemental information.

### Known drug reactions and interaction with other therapies

In new-onset T1D subjects, no concerning safety signals were seen in low dose (2.5 mg/kg) ATG-treated subjects (12–45 years) in a 1-year trial with 5-year follow-up, as reported by Haller *et al*.^25 26 29^ Predominant AEs reported include serum sickness, CD4 lymphocyte decrease, CRS, fever, influenza-like symptoms and rash. Serum sickness was observed in the majority of participants (72.4%) who received low dose ATG, but this was predictable and short-lived. In addition, none of the participants required extended hospitalisation or readmission due to CRS or serum sickness, and no cases of grade 4 serum sickness or CRS were reported.

In MELD-ATG, premedication described in the MELD-ATG Pharmacy Manual will be given to all participants to minimise the risk of these side effects, and participants will be closely monitored. None of the participants who received low dose ATG in this previous trial developed a serious infection. Infection screening is part of the screening and baseline assessments for MELD-ATG, to ensure individuals with infections are not given ATG.

Management of serum sickness, CRS and haematological effects in MELD-ATG are provided below. The safety and effectiveness of ATG in new onset T1D paediatric participants <12 years needs confirmatory further study in controlled trials. However, for the approved indications (at a higher total dose than 2.5 mg/kg), data based on limited European studies and compassionate use in US indicates that the dose, adverse reaction (AR) profile and efficacy are not different than that reported in adolescents and adults. Known reactions to ATG in the licenced indications are described in the SmPC.^22^

No drug interaction studies with ATG have been reported^33^; however, certain groups of medications are contraindicated for reasons other than interaction with ATG. The following would interfere with interpretation of the trial and should be avoided throughout: (1) agents that influence insulin sensitivity or secretion (eg, pramlintide, sulfonylureas, metformin, diphenylhydantoin, thiazide or other potassium-depleting diuretics, β-adrenergic blockers, niacin), (2) any medication that may result in immunosuppression or immunomodulation and (3) systemic glucocorticoids (except when required as premedication for ATG/placebo administration or for the treatment of CRS or serum sickness). If participants receive, or if the investigator believes that participants must receive, any of these medications, it must be documented in the source data and eCRF, as per other concomitant medications. For the participant’s safety, live vaccinations should be avoided from within ≥6 weeks prior to treatment day 1 until 6 months post-treatment, as stated in the eligibility criteria. Killed vaccines are permitted. Drugs not listed above will be also permitted as per investigators’ discretion and should be listed in the eCRF.

### Advice on SARS-CoV-2/COVID-19 for the MELD-ATG trial

The MELD-ATG team are constantly revising our advice in a prepared COVID-19 bulletin on COVID-19 as the situation changes. The most up to date version of our COVID-19 bulletin can be accessed by contacting the MELD-ATG office ([contact] and/or [contact]).

### Concomitant treatments

Concomitant medications will be assessed at each trial visit. Usual treatment with insulin, either via multiple injections or pump therapy, will be continued during the trial as advised by the investigator or other medical professional responsible for the participant’s standard-of-care insulin therapy. Exceptions where adapted insulin regimens may be required are the MMTTs and DBS home collections. The use of non-insulin pharmaceuticals that affect glycaemic control will not be allowed for the trial duration.

### Compliance with trial treatment

Participants are treated under strict medical supervision, with the trial treatment being administered by healthcare professionals. Compliance with treatment may be assessed by referring to medication administration records and any remaining unused ATG/placebo after treatment has been stopped, which should be returned to the site pharmacy for reconciliation.

### Dose delays and missed doses

Following review of the FBC obtained following completion of the first trial treatment (ATG or placebo) infusion, the dose of the second infusion may be reduced by 50% in certain scenarios.

### Evaluation of AEs

Sponsor expects that AEs are recorded from the point of written informed consent/assent regardless of whether a participant has yet received a medicinal product. Individual AEs should be evaluated by the investigator. This includes the evaluation of its seriousness, and any relationship between the IMP(s) and/or concomitant therapy and the AE (causality). More information on the definitions for assessment of safety in MELD-ATG can be found in online supplemental information.

Assessment of seriousness defines whether the event is an AE, serious AE (SAE) or an Serious adverse reaction (SAR). Assessment of causality is broken up into the following categories: (1) Definitely: A causal relationship is clinically/biologically certain. This is therefore an AR; (2) Probable: A causal relationship is clinically/biologically highly plausible and there is a plausible time sequence between onset of the AE and administration of the IMP and there is a reasonable response on withdrawal. This is therefore an AR; (3) Possible: A causal relationship is clinically/biologically plausible and there is a plausible time sequence between onset of the AE and administration of the IMP. This is, therefore, an AR (4) Unlikely: A causal relation is improbable and another documented cause of the AE is most plausible. This is therefore an AE; (5) Unrelated: A causal relationship can be definitely excluded and another documented cause of the AE is most plausible. This is therefore an AE. Unlikely and unrelated causalities are considered not to be IMP related. Definitely, probable and possible causalities are considered to be IMP related. A pre-existing condition must not be recorded as an AE or reported as an SAE unless the condition worsens during the trial and meets the criteria for reporting or recording in the appropriate section of the eCRF.

All events should be graded for severity according to the NCI-CTCAE Toxicity Criteria (V.5.0).

AEs and ARs should be recorded in the medical notes and the appropriate section of the eCRF. SAEs and SARs should be reported to the Sponsor and IMP manufacturer as detailed below.

### Expected AEs/SAE

The following are (S)AEs that could be reasonably expected for this trial population during the course of the trial. These events are exempt from being reported as SAEs and will be recorded in the eCRF only: (1) diabetic ketoacidosis, (2) hospital admissions related to diabetes (planned and unplanned) and (3) hypoglycaemic event which requires assistance from a third party.

The following AEs are known side effects of participating in this trial. They are generally not serious in nature and will not be recorded in the eCRF: (1) injection site and mild skin reactions following IV administration of ATG/placebo, (2) mild bruising at venipuncture site, (3) mild reaction to plasters and (4) vasovagal response during venipuncture.

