### Randomisation

Prior to randomisation and treatment, the investigator or design will review baseline data to reconfirm that the participant is safe to receive trial treatment and continues to fulfil the eligibility criteria. Randomisation should be performed before the participant is due to receive their first trial treatment infusion, allowing sufficient time for treatment preparation. Randomisation should only occur for whom the eligibility criteria can be confirmed.

### Treatment day 1 and 2

Participants will be under strict medical supervision in hospital for the treatment visit. The total dose of trial treatment will be given over two consecutive days by intravenous infusion.

Treatment day 1 will be ≤6 ±3 weeks from T1D diagnosis. Changes to health and medications since the baseline visit should be checked including a SARS-CoV-2 test, and blood pressure, heart rate, oxygen saturation, respiratory rate and temperature will be recorded. The participant should also be physically examined for evidence of current infection prior to administration of premedication. It is recommended that concomitant medication with heparin and hydrocortisone, and premedication with corticosteroid, antihistamine and acetaminophen, is given as described in the MELD-ATG Pharmacy Manual, to limit ARs from peripheral ATG/placebo infusion. Blood glucose levels may be affected by premedication and will be managed by the responsible investigator.

The first part-dose of 0.5 mg/kg or 0.1 mg/kg ATG, or placebo of the same volume, will be given as an intravenous infusion over a minimum of 12 hours. AEs throughout the infusion until the end of the visit will be recorded. At the end of the infusion, blood will be collected for FBC, clotting studies (PT and APTT), if PT and/or APTT were abnormal but not beyond exclusion criteria at the screening visit, as well as renal and liver function. The FBC will be reviewed in order to confirm that it is safe to continue with the second treatment infusion.

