### Reporting SAEs

Each principal investigator (PI) must record all AEs and report SAEs in English to the Clinical trial Coordinating centre (CTCC) in Cambridge, using the trial-specific SAE form, within 24 hours of their awareness of the event; the sponsor must then immediately forward the form to Sanofi. The co-ordinating centre will perform an initial check of the report, request any additional information, and will pass it on to the chief investigator (CI) or nominated clinician without delay.

The CI is responsible for the onward notification of all SAEs to the sponsor immediately but not more than 24 hours of first notification. A detailed record of all SAE’s reported to the sponsor will be kept. The CI is also responsible for prompt reporting of all SAE findings to the competent authority if they could: (1) adversely affect the health of participants, (2) impact on the conduct of the trial, (3) alter the risk to benefit ratio of the trial, (4) alter the competent authority’s authorisation to continue the trial in accordance with Directive 2001/20/EC. PIs will be informed of all suspected unexpected serious adverse reactions (SUSARs) and will ensure it is reported to their relevant authorities in accordance with their own regulations.

SAEs will also be reported to the IMP manufacturer in accordance with the pharmacovigilance agreement and be reviewed at the next IDMC meeting.

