### Reporting of suspected unexpected serious adverse reactions

All suspected ARs related to an IMP (the tested IMP and comparators) which occur in the concerned trial, and that are both unexpected and serious (SUSARs) are subject to expedited reporting. Each PI must notify all SUSARs, in English, to the CTCC in Cambridge, using the trial-specific SAE form, immediately as they become aware of the event.

The CI must report all the relevant safety information previously described, to the: (1) sponsor, (2) competent authorities in the concerned member states, (3) Ethics Committee in the concerned member states and (4) IMP manufacturer. The CI shall inform all investigators concerned of relevant information about SUSARs that could adversely affect the safety of participants.

For fatal or life-threatening SUSARs, all parties listed in the paragraph above must be notified as soon as possible but no later than seven calendar days after the trial team and sponsor has first knowledge of the minimum criteria for expedited reporting. In each case, relevant follow-up information should be sought and a report completed as soon as possible. It should be communicated to all parties within an additional eight calendar days. Non-fatal and non-life-threatening SUSARs must be reported as soon as possible but no later than 15 calendar days after first knowledge of the minimum criteria for expedited reporting. Further relevant follow-up information should be given as soon as possible.

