Other allergic reactions to trial treatment infusion may be managed based on the severity of the allergic reaction. A mild (≤grade 1–2) allergic reaction will allow trial medication to be restarted at the discretion of the investigator. With either a severe (grade 3) reaction or a life-threatening (grade 4) allergic reaction, trial medication should be permanently discontinued. In case of anaphylaxis (begins at CTCAE grade 3 or higher), the trial treatment infusion should be terminated immediately, and appropriate emergency treatment should be initiated. Equipment for emergency therapy for anaphylactic shock must be readily available.

Serum sickness from host immunisation against rabbit protein may occur 7–15 days after the first dose of ATG. It is a reaction that is similar to an allergy. Signs and symptoms can take as long as 14 days after exposure to appear, and may include signs and symptoms commonly associated with hypersensitivity or infections including rashes, itching, arthralgia (especially finger and toe joints), fever (as high as 40°C and usually appears before rash), lymphadenopathy (particularly near the site of injection, head and neck), malaise, hypotension, splenomegaly, glomerulonephritis, protein or blood in the urine or shock. The participants than may require glucocorticoid treatment for supportive care. The dose will depend on the severity of signs and symptoms and guidance is provided in the MELD-ATG Trial Manual. The least amount of steroid required to provide symptomatic relief of serum sickness, due to the effect of glucocorticoid on blood glucose.

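### The SAE exemption for diabetes events has no exception for related, life-threatening or fatal cases and conflicts with the protocol's own SAR, SAE and SUSAR reporting rules

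*Protocol article*

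**What the plan says.** The section Expected AEs/SAE introduces three event types with "The following are (S)AEs that could be reasonably expected for this trial population during the course of the trial". They are diabetic ketoacidosis, any diabetes-related admission whether planned or not, and assisted hypoglycaemia. The rule that follows is "These events are exempt from being reported as SAEs and will be recorded in the eCRF only". No condition on causality, timing, severity or outcome is attached.

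Three neighbouring rules bear on the same events:

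- **Evaluation of AEs.** The investigator judges the seriousness of each AE and its relation to the IMP or concomitant therapy. Events classed as possible, probable or definite are adverse reactions; unlikely and unrelated ones are not. Then: "SAEs and SARs should be reported to the Sponsor and IMP manufacturer as detailed below".
- **Reporting SAEs.** Each principal investigator reports SAEs to the coordinating centre within 24 hours of awareness. In addition, "SAEs will also be reported to the IMP manufacturer in accordance with the pharmacovigilance agreement and be reviewed at the next IDMC meeting".
- **The SUSAR section (Reporting of suspected unexpected serious adverse reactions).** The expedited duty covers "All suspected ARs related to an IMP (the tested IMP and comparators) which occur in the concerned trial" where the reaction is both serious and unexpected. The limit is 7 calendar days if fatal or life-threatening and 15 otherwise. The exemption is not mentioned.

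**The concern.** Exempting common disease events from SAE reporting is an ordinary choice in a diabetes trial. The difficulty is that this exemption is defined only by what the event is. The other three rules depend on what caused it and how it ended. For a related, life-threatening or fatal case, the rules give different answers.

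A related case is conceivable on the protocol's own account. On premedication, Treatment day 1 and 2 says: "Blood glucose levels may be affected by premedication and will be managed by the responsible investigator". Toxicity management allows glucocorticoids for serum sickness and asks for the least amount, "due to the effect of glucocorticoid on blood glucose". The section on trial participants and oversight adds that ATG has not yet been used in this indication and at these doses in children aged 5–11.

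At stake is the prompt, individual report. Recruitment is not halted between cohorts (Interim analyses) and there are no statistical conditions for stopping (Criteria for the premature termination of the trial). Early notice of a serious metabolic event therefore depends largely on single-case reporting.

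**Working it through.** No figure is stated or disputed, so the check sets the rules side by side. Take a ketoacidosis that meets the criteria for a serious event and follow it through each section.

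| Case | Expected AEs/SAE | Evaluation of AEs and Reporting SAEs | SUSAR section | Outcome |
|---|---|---|---|---|
| Unrelated, neither fatal nor life-threatening | eCRF only | 24-hour SAE report unless exempted | Does not apply | The exemption works as presumably intended |
| Unrelated, fatal | eCRF only | 24-hour SAE report, next IDMC meeting | Does not apply (not a reaction) | SAE route lost if the exemption is followed |
| Possibly related, not life-threatening | eCRF only | SAR to sponsor and manufacturer | 15 days if unexpected for the IMP | Contradictory instructions |
| Possibly related, fatal or life-threatening | eCRF only | SAR to sponsor and manufacturer, 24-hour report | 7 days if unexpected for the IMP | Contradictory instructions |

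Only the first row is free of difficulty.

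The next question is whether the SUSAR rule dependably rescues the last two rows. Three features of the text make that doubtful:

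1. The SUSAR section starts the clock for an event assessed as serious and unexpected, while the exempt events stand under a heading that calls them expected. That expectedness refers to the trial population. Expectedness for the IMP is a different question, and the article does not separate the two.
2. SUSARs are notified on the trial-specific SAE form, which is the form the exemption tells the site not to use for these events.
3. Authorisation of participating sites has the principal investigator assess causality and expectedness for SAEs. A site that does not handle the event as an SAE may not make the expectedness assessment at all.

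The last question is what remains if a site follows the exemption. The event is still in the eCRF. Table 1 includes AEs by dosage group in the safety outcome. The IDMC and DDC review the safety data when middle doses are chosen (Trial participants, study design and oversight; Figure 1 legend). The IDMC advises on the basis of interim analyses and safety endpoints (IDMC and DDC), and the DDC reviews safety outcomes by age at each of six interim analyses (Interim analyses). The information can therefore still reach both committees. What is lost is the 24-hour report and review as an individual SAE at the next IDMC meeting.

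**The case against.** The strongest reply has four parts.

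**No route is closed.** A reader might infer that a related or fatal case never enters the SUSAR or IDMC route. The documents do not support that. The SUSAR rule is not made subject to the exemption, serious adverse reactions have their own reporting sentence, and the exemption speaks only of reporting as SAEs. The interim reviews reach the eCRF data. Ketoacidosis is also asked about at every follow-up visit (Subsequent assessments: follow-up visits 1–6). This part stands: the defect is a conflict between instructions and a possible delay.

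**A steroid effect is not clearly an IMP reaction.** The causality categories and the SUSAR rule are framed around the IMP, and premedication requirements are the same on placebo (Placebo section). This stands in part. The glucose statements show that a treatment-related event is conceivable; they do not show that it would be a SUSAR. Evaluation of AEs does, however, ask the investigator to consider concomitant therapy as well.

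**The size is unknown.** A reader might multiply the 72.4% serum sickness rate reported for low-dose ATG by the 32 planned at 2.5 mg/kg. That would count serum sickness in a trial of people aged 12–45. It would not count steroid use, ketoacidosis or admissions. The same section describes those cases as short-lived, with no extended stay or readmission. Nor do the documents establish a dose gradient in the exempt events, or an under-count in an SAE table by arm, which the article does not specify.

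**The article is condensed.** Evaluation of AEs sends further safety definitions to online supplemental information, and a protocol appendix is listed under Extended data. Neither is shown, and an exception could be there. This lowers confidence but does not answer the point, because the exemption is printed as a complete and unqualified rule.

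**Conclusion.** The point holds as an internal conflict. The exemption has no exception for events judged related to trial treatment, or for fatal or life-threatening ones, and for those cases it cannot be followed together with the sections on AE evaluation, SAE reporting and SUSARs. Followed literally, it removes the 24-hour individual report and the next-meeting IDMC review for three event types. It also leaves a site unsure whether the 7-day or 15-day clock applies. A fatal but unrelated case loses only the SAE route.

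The number of participants affected cannot be estimated from the documents and may be small. The conclusion assumes that sites may read the words expected and eCRF only as overriding the other sections, and that the supplement, which is not shown, contains no exception. Confidence is therefore moderate. The wording should be changed because prompt safety reporting is involved and the change is cheap.

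**What to change.** Reconcile Evaluation of AEs, Expected AEs/SAE, Reporting SAEs and the SUSAR section by stating that:

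1. The exemption applies only to listed events that the investigator assesses as unlikely or unrelated under the categories in Evaluation of AEs, and that are neither fatal nor life-threatening.
2. All other listed events follow the SAE and SUSAR sections. It should be made clear whether relatedness here includes concomitant therapy, which Evaluation of AEs already asks about.
3. Being expected in the trial population does not decide whether an event is expected for the IMP.

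The events that stay exempt should be shown by arm and age in the interim safety reports already planned for the IDMC and DDC. If the supplement already contains such a limit, a cross-reference in Expected AEs/SAE is enough.

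The cost is a wording amendment and a few extra SAE forms. The interim display uses data already in the eCRF.

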1. To determine the effects of ATG treatment on stimulated C-peptide	1. The area under the stimulated C-peptide response curve over the first 2 hours of an MMTT measured throughout the study in different ATG dosage groups	1. Baseline, 3, 6, 12 months
2. To determine the effects of ATG treatment on HbA1c	2. HbA1c measurements measured throughout the study in different ATG dosage groups in mmol/mol	2. Baseline, 3, 6, 12 months
3. To determine the effects of ATG treatment on intermittent CGM measures	3. CGM measures (time in range, time above, time below) measured throughout the study in all different ATG dosage groups and placebo	3. For 14 days at 3, 6, 12 months
4. To determine the effects of ATG treatment on fasting and stimulated DBS C-peptide measurements	4. DBS C-peptide measurements measured throughout the study in all different ATG dosage groups and placebo in pmol/L at 0 min and 60 min	4. Baseline, monthly
5. To determine whether ATG treatment mediates a reduction in CD4-positive T cells but relative preservation of CD8-positive T cells	5. CD4-positive T cells and CD8-positive T cells measured throughout the study in different dosage groups	5. Baseline, 1, 2, 4 weeks and 3, 6, 12 months
6. Descriptive analysis of the safety profile of different doses of ATG in different age groups	6. Safety will be assessed at each visit by physical examination, including assessment of the most commonly reported reactions to ATG, namely serum sickness, CD4 + lymphocyte decrease, cytokine release syndrome, fever, influenza-like symptoms and rash; vital signs (temperature, blood pressure, heart rate); weight, abnormal laboratory parameters (liver, kidney function, full blood count); reporting of adverse events in different dosage groups	6. Baseline, treatment day 1 and 2, 1, 2, 4 weeks and 3, 6, 12 months
7. To determine the effects of ATG treatment on T1D-associated autoantibodies (GADA, IAA, IA-2A and ZnT8A)	7. T1D-associated autoantibodies (GADA, IAA, IA-2A and ZnT8A) at the start and end of the study	7. Screening, 12 months
8. To determine the effects of ATG treatment on insulin requirements	8. Insulin requirements measured throughout the study in all different ATG dosage groups	8. Baseline, 1, 2, 4 weeks and 3, 6, 12 months
Exploratory objectives		

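### As worded, the eCRF exemption for mild skin reactions after infusion can leave isolated mild rash out of a safety outcome that names rash

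*Protocol article*

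**What the plan says.** Expected AEs/SAE ends with a short list of side effects regarded as generally not serious, which "will not be recorded in the eCRF: (1) injection site and mild skin reactions following IV administration of ATG/placebo". The other items are mild bruising at the venepuncture site, mild reactions to plasters, and vasovagal response during venepuncture.

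Table 1 (Objectives) sets secondary objective 6 as "Descriptive analysis of the safety profile of different doses of ATG in different age groups". Its outcome is assessed at each visit by physical examination, which includes the commonest reactions to ATG, "namely serum sickness, CD4 + lymphocyte decrease, cytokine release syndrome, fever, influenza-like symptoms and rash", and it ends with "reporting of adverse events in different dosage groups".

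Known drug reactions and interaction with other therapies says of earlier low-dose ATG experience: "Predominant AEs reported include serum sickness, CD4 lymphocyte decrease, CRS, fever, influenza-like symptoms and rash". It gives no rate for rash.

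On recording in general, Evaluation of AEs says "AEs and ARs should be recorded in the medical notes and the appropriate section of the eCRF", and Reporting SAEs says "Each principal investigator (PI) must record all AEs". Data management and eCRF makes the eCRF the place where all trial data are collected.

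**The concern.** One section keeps a class of skin event out of the trial database, and another makes rash a named element of a safety outcome to be described by dose and age. Nothing in the article defines a mild skin reaction so as to separate it from rash, and nothing says that rash falls outside the exemption.

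The trial looks for the lowest effective dose, so the picture of reactions at each dose matters to how its result is used. The Dose Determining Committee also relies on safety data during the trial: for the step down to ages 5–11 (Trial participants, study design and oversight), and when it reviews safety outcomes by age at each interim analysis (Interim analyses). An event type that some sites enter and others leave out weakens these comparisons and may be hard to recover afterwards.

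**Working it through.** The point rests on the text; no figure in the article has to be reproduced. The passages are set side by side first, and an illustration then tests whether a direction of bias can be claimed.

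**Text**

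1. *Does the exemption reach beyond the infusion site?* Item (1) names injection-site reactions and then adds mild skin reactions after IV administration. Local effects of venepuncture and plasters have their own items. If only local reactions were meant, the added words would do little work. There is also no time limit on what counts as following administration.
2. *Is rash part of an outcome?* Yes. Table 1 names it under objective 6, by dose and age group.
3. *Which rash stays recordable?* Toxicity management lists rash as a sign of cytokine release syndrome, of hypersensitivity and of serum sickness. None of these is exempt. What the exemption can remove is a mild rash that a site does not attribute to any of them.
4. *Is there another route into the data?* Table 2 schedules a physical examination on both treatment days, at 1, 2 and 4 weeks, and at 3, 6 and 12 months. A rash present at a visit may be noted there. A short-lived rash between visits depends on adverse event recording. The article describes no route for either to the analysis other than the eCRF.

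**Illustration of size and direction**

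The article gives neither rash rates nor the share of rash that is mild, so every rate and share below is an assumption. The 32 per arm is the planned number for placebo and for 2.5 mg/kg (sample size section). The worst case is taken: every mild rash goes unrecorded.

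Recorded rate = true rate × (1 − mild share). Events lost = 32 × true rate × mild share.

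*Same mild share in both arms, true rates 10% (placebo) and 40% (ATG):*

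| Mild share | Recorded rates | Recorded difference (true: 30 points) | Events lost, placebo / ATG | Risk ratio |
|---|---|---|---|---|
| 25% | 7.5% / 30% | 22.5 | 0.8 / 3.2 | 4.0 |
| 50% | 5% / 20% | 15.0 | 1.6 / 6.4 | 4.0 |
| 75% | 2.5% / 10% | 7.5 | 2.4 / 9.6 | 4.0 |

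The absolute loss is larger on ATG and the risk difference shrinks, but the risk ratio stays at its true value of 40/10 = 4.0.

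*Rash more severe at the higher dose, true rates 10 / 30 / 50% (placebo / low / high), mild shares 90 / 90 / 50%:*

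- Points lost: 10 × 0.9 = 9; 30 × 0.9 = 27; 50 × 0.5 = 25.
- Recorded rates: 1 / 3 / 25%.
- High minus placebo: 40 points true, 25 − 1 = 24 recorded. This gap shrinks.
- High minus low: 20 points true, 25 − 3 = 22 recorded. This gap widens.

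The largest absolute loss now falls on the low dose, and the proportional loss is smallest at the high dose. The direction depends on a severity split that the article does not give.

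**The case against.** The strongest reply is that the exemption is about local irritation. Its neighbours in the list are all local or procedural, and Infusion site management describes infusion-site reactions as relatively common with both active drug and placebo. In that setting mild skin reactions may simply mean redness around the cannula. This reading is possible, and it may be what was intended. It does not settle the matter, because the words go further than injection-site reactions and no section shown takes rash out of the exemption.

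Second, most rash of clinical interest should be captured as part of a named syndrome, and rash is looked for at each visit. Both points stand. They confine the gap to isolated mild rash and make under-recording a possibility, not a certainty.

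Third, the general rule on recording adverse events might be thought to contradict the exemption. A reader could infer that from Evaluation of AEs and Reporting SAEs, but a specific exemption that qualifies a general rule is ordinary drafting. The tension that matters is with rash as a named outcome in Table 1.

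Fourth, the article refers to online supplemental information and a Trial Manual that are not shown, and the boundary may be drawn there. If so, the fix amounts to carrying that boundary into the section that states the exemption.

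**Conclusion.** The point holds as a wording conflict with a limited consequence. Followed as written, the exemption allows an isolated grade 1 rash after infusion to be left out of the eCRF, although rash is named in secondary safety outcome 6 and is a predominant reaction to low-dose ATG. The descriptive safety profile by dose and age, and the safety data put before the Dose Determining Committee, could then be incomplete or uneven for mild rash.

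This rests on the plain reading of the exemption and on the rash not being recorded under a named syndrome. Its size cannot be estimated from the article.

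Three stronger conclusions are tempting but not supported:

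- That rash will certainly be under-counted. The visit examinations and the local-reaction reading leave this open.
- That the loss is greatest where ATG causes rash, so that the dose gradient is flattened. This holds for absolute counts if the mild share is similar across arms, but not for the risk ratio, and not in general if severity rises with dose.
- That the loss can be expressed as reduced power to detect a difference in rash. Objective 6 is descriptive, no such test is planned, and the rates would have to be assumed.

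**What to change.** Reconcile the exemption in Expected AEs/SAE with outcome 6 in Table 1. Limit item (1) to local reactions at the infusion or venepuncture site, and add a sentence that non-local rash of any CTCAE grade is recorded in the eCRF with its onset date, whether or not it is attributed to a named syndrome.

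This changes data collection only and leaves the management of reactions untouched. It costs a wording change, a short note to sites and a few more adverse event entries. It is best done early, because mild events that were never entered may not be recoverable.
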